| Study Products                        | Autologous, ex vivo expanded natural regulatory T cells (Tregs)                                                                                                               |
| Duration of administration            | Single infusion of expanded Tregs day +60 following living donor kidney transplantation                                                                                       |
| Statistical Methodology               | Mann-Whitney, Fisher test, Student’s t test, Anova and Chi-Squared analyses will be used to analyze the safety data as needed.                                                |

ESTIMATED ENROLLMENT: 12

STUDY START DATE: MARCH 2014

ESTIMATED STUDY COMPLETION: MARCH 2016

ESTIMATED PRIMARY COMPLETION DATE: APRIL 2015

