### TREATMENT SCHEMA

EXPERIMENTAL: TRACT (N=12)  
AUTOLOGOUS TREG INFUSION

Kidney transplantation using standard of care immunosuppressive agents will be performed, followed by intravenous infusion of autologous, expanded Tregs (TRACT) at day 60 after transplantation. Subjects will be administered only one dose of Treg at the specified dose level. Cell infusions will be escalated in the absence of adverse events within 30 days of infusion using the following schema:

Tier 1:  $0.5 \times 10^9$  total expanded nTregs (n=3)

Tier 2:  $1 \times 10^9$  total expanded nTregs (n=3)

Tier 3:  $5 \times 10^9$  total expanded nTregs (n=3)

Tier 4:  $8 \times 10^9$  total expanded nTregs (n=3)

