### **1.9 Approach**

We propose to use our knowledge gained from small animal and preclinical human studies to embark on an investigational pathway for clinical application of ex vivo expanded human nTregs as adoptive cellular therapy (TRACT). This is both extremely innovative and potentially very significant – TRACT with recipient derived Tregs could allow for significant reduction and perhaps elimination of immunosuppressive medications in organ transplantation. Although TRACT with ex-vivo manipulated Tregs have recently been initiated in the context of stem cell transplantation for the prevention of graft versus host disease, our clinical trial represents the first use of recipient-derived Tregs in an adult kidney transplant setting. In this proposal, we will conduct a phase 1 trial of TRACT in 12 recipients of HLA mismatched living donor renal transplants. In order to reach our target number of subjects that are needed to complete the study, we plan to recruit and consent up to 20 subjects, as we anticipate either screen failure or withdrawal from the study is a possibility prior to initiation of study involvement. Initiation of study involvement is defined as the administration of the Treg cellular product (study drug). As Northwestern University has the largest living donor transplant program in North America (~ 160 patients per year) we are confident in our ability to recruit and enroll the patients required for this study in a timely manner.

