A dose-limiting toxicity (DLT) is defined as a clinically significant adverse event or abnormal laboratory value assessed as unrelated to the kidney transplant, intercurrent illness, or concomitant medications and occurring during the first 3 weeks after administration of the first dose that meets any of the following criteria: grade 3 or 4 non-hematologic toxicity (except for electrolyte disturbances responsive to correction measures within 48h, diarrhea, nausea and vomiting that responds to standard medical care, rash  $\geq$  Grade 3 that response to supportive care, infusion relation reaction that are responsive to supportive care, infections and infectious complications related to patients neutropenia, elevated creatinine  $<3.5 \times$  upper limit of normal, elevated AST  $< 8 \times$  upper limit of normal, elevated ALT  $<8 \times$  upper limit of normal, elevated bilirubin  $< 5 \times$  upper limit of normal, elevated PTT  $< 3.5 \times$  upper limit of normal).

Dose escalation will only occur after patients, at a given dose level, have been followed for at least 21 days and no evidence of dose limiting toxicity has been seen. The dose level for a given patient and the progression of doses from one cohort of patients to the next will be adjusted based on adverse events. If a patient is discontinued due to concurrent illness unrelated to toxicity or organ rejection before they reach the end of the treatment cycle (21 days after the infusion), an additional patient will be enrolled at that same dose level.

| No. of Patients with DLT at a Given Dose Level | Escalation Decision Rule                                                                                                                                                                                                                                              |
|------------------------------------------------|-----------------------------------------------------------------------------------------------------------------------------------------------------------------------------------------------------------------------------------------------------------------------|
| 0 out of 3                                     | Enter patient(s) at the next dose level.                                                                                                                                                                                                                              |

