| $\geq 2$                                       | Dose escalation will be stopped. This dose level will be declared the maximally administered dose (highest dose administered). Three additional patients will be entered at the next lowest dose level if only 3 patients were treated previously at that dose level. |
| 1 out of 3                                     | Enter at least 3 more patients at this dose level. 
 
If 0 of these 3 patients experience DLT, proceed to the next dose level.
 
                                                                                         |

|                                                                          |                                                                                                                                                                                                                                                                                                                      |
|--------------------------------------------------------------------------|----------------------------------------------------------------------------------------------------------------------------------------------------------------------------------------------------------------------------------------------------------------------------------------------------------------------|
|                                                                          | 
 
If 1 or more of this group suffer DLT, then dose escalation is stopped and this dose is declared the maximally administered dose. Three additional patients will be entered at the next lowest dose level if only 3 patients were treated previously at that dose.
 
 |
| ≤ 1 out of 6 at highest dose level below the maximally administered dose | This will be the Maximum Tolerated Dose (MTD). At least 6 patients will be entered at this dose.                                                                                                                                                                                                                     |

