Once a cohort is filled, enrollment into the next dose level will only begin after all patients in that cohort have passed through the DLT observation period. At that point, the PI, IND Sponsor, IND Medical Monitor and study co-investigators will review toxicity reports and recommend whether or not it is safe to proceed to the next cohort.

After escalation has stopped, de-escalation will begin at one dose level below the maximum achieved during escalation. The action taken depends on the number of patients previously treated at a dose level. If 3 or fewer patients have previously been treated, 3 patients are added; if 6 patients have previously been treated, this level will be declared to be the MTD. The MTD is defined to be the highest dose level at which no more than 1 of 6 treated patients experiences a DLT.

Patients within a cohort need not be accrued or treated at the same time; thus, accrual at a dose level should stop as soon as 2 patients at a dose level have experienced DLT at that level. There will be no intra-patient dose escalation or de-escalation.

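### The stated size of 12 treated (3 per tier) conflicts with the cohort rules of section 7.4, and no path through all four tiers can yield an MTD within 12

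*Protocol*

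**What the plan says.** **Size.** The Study Summary gives 12 subjects and "ESTIMATED ENROLLMENT: 12". The Treatment Schema gives N=12 and n=3 for each of the four tiers, and section 4.1 repeats n=3 per tier. Section 1.9 says "we will conduct a phase 1 trial of TRACT in 12 recipients of HLA mismatched living donor renal transplants". It adds that "we plan to recruit and consent up to 20 subjects", because screen failure or withdrawal before infusion is possible.

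**Cohort rules (section 7.4).**
- 0 of 3 with a DLT: "Enter patient(s) at the next dose level".
- 1 of 3: at least three more patients at that level. Go up if none of the added three has a DLT; otherwise stop.
- 2 or more: stop, and add three at the level below if it holds only three.
- At most 1 of 6, at the highest level below the maximally administered dose: "This will be the Maximum Tolerated Dose (MTD). At least 6 patients will be entered at this dose".

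The text after the table repeats the requirement: "The MTD is defined to be the highest dose level at which no more than 1 of 6 treated patients experiences a DLT". It also stops accrual at a level once two patients there have had a DLT. A patient discontinued within 21 days of infusion because of concurrent illness is replaced at the same level.

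**The concern.** The two parts of the protocol describe trials of different size. Twelve allows for no cohort expansion, no de-escalation cohort and no tier of six, yet section 7.4 prescribes all three. No passage calls 12 a minimum or a DLT-free scenario, and the allowance up to 20 covers losses before infusion, not expansion.

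The Study Summary calls the trial dose-finding, section 7.4 defines an MTD, and section 2.3 says the data will support later phase 2 trials. If the product is well tolerated, a trial run at its stated size ends with three patients on the top tier and no MTD under its own definition. If a DLT occurs, following section 7.4 may take the trial past its stated enrolment.

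**Working it through.** **Inputs from the protocol.** Four dose levels; three per tier; 12 treated; up to 20 consented; the section 7.4 rules above. The protocol gives no DLT rate, so flat per-patient rates of 5%, 10% and 20% are assumed.

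**1. The plan's own figure.** 4 × 3 = 12. It is reproduced, as the path with no expansion.

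**2. Paths that complete Tier 4.** Twelve patients over four completed tiers means three in each, so no tier has six and none can be an MTD.
- No DLT: 3 + 3 + 3 + 3 = 12, no MTD. The table sends 0 of 3 at Tier 4 to a next level that is not there, and the MTD row speaks only of a level below the maximally administered dose.
- One tier expanded after 1 of 3, the others 0 of 3: 6 + 3 + 3 + 3 = 15.
- All four tiers at six: 4 × 6 = 24, before replacements and before any use of the words allowing more than three added patients.

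**3. Paths that stop earlier (full cohorts).**
- Stop at Tier 1: 3 or 6 treated, no MTD.
- Stop at Tier 2, MTD at Tier 1: 9 or 12.
- Stop at Tier 3: an MTD is possible with 12 (3 + 3 + 3 + 3 added at Tier 2, or 3 + 6 + 3), otherwise with 15 or 18.

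**4. Hand check at a 5% DLT rate.** For three patients: P(0) = 0.95³ = 0.8574; P(1) = 3 × 0.05 × 0.95² = 0.1354; P(2 or more) = 0.00725.
- A tier passes with 3: 0.8574.
- A tier passes with 6: 0.1354 × 0.8574 = 0.1161.
- A tier fails: 0.00725 + 0.1354 × (1 − 0.8574) = 0.0266.
- Stop at Tier 2, MTD at Tier 1: 0.8574 × 0.0266 × 0.9928 + 0.1161 × 0.0266 = 0.0257. Here 0.9928 = P(0) + P(1), the chance that the three added patients leave at most 1 of 6.
- Stop at Tier 3, MTD at Tier 2, total 12: 0.8574² × 0.00725 × 0.9928 + 0.8574 × 0.1161 × 0.00725 = 0.0060.
- MTD within 12: 0.0257 + 0.0060 = 0.0317, about 3%.
- Treated 12 or fewer: 0.95¹² (0.5404) + stop at Tier 1 (0.0266) + MTD within 12 (0.0317) + stop at Tier 2 with Tier 1 then failing (0.8574 × 0.0266 × 0.00725 = 0.0002) = 0.5989.
- Treated more than 12: 1 − 0.5989 = 0.401, about 40%.

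**5. Full enumeration of the rules as written** (nobody added at Tier 4 after 0 of 3):

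| Flat DLT rate | No DLT in 12 | MTD within 12 treated | More than 12 treated |
|---|---|---|---|
| 5% | 54% | 3% | 40% |
| 10% | 28% | 10% | 52% |
| 20% | 7% | 23% | 40% |

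Stopping accrual at the second DLT lowers some totals (for example 3 + 3 + 6 + 2 = 14) but leaves these percentages unchanged.

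**6. Consents.** 20 − 15 = 5 and 20 − 18 = 2, so 15 or 18 treated fit if no more than 5 or 2 consented patients are lost before infusion. Totals of 21 or 24 exceed 20.

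**7. What 0 of 3 supports.** The exact two-sided 95% upper bound is 1 − 0.025^(1/3) = 70.8%.

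**The case against.** **The objective is safety.** Sections 3.1 to 3.3 name no MTD, and section 7.6.1 tabulates toxicities and describes DLTs patient by patient. A DLT-free run of 12 would meet that objective, the 12 is labelled an estimate, and nothing bars expansion beyond it. This stands: neither the primary objective nor a safety rule fails. It does not remove the conflict, because section 7.4 still defines an MTD and prescribes the expansions.

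**Stronger readings that the documents do not support.**
- A reader might infer that section 7.4 always needs 15 to 24 treated, so that 12 can never give an MTD. It can, with 9 or 12, when escalation stops at Tier 2 or 3.
- A reader might infer that section 7.4 requires 15 when no DLT occurs. That figure is inferred from the six-patient definition. The MTD row is conditional on a level below the maximally administered dose, and no sentence adds patients at Tier 4 after 0 of 3. The section is silent there.
- A reader might infer that any single DLT breaks the 12. It need not: 3 + 6 + 3 = 12 if Tier 2 expands and escalation then stops at Tier 3.
- A reader might treat 12 of 20 as a planned yield and scale the consents up. Section 1.9 gives a ceiling, not a yield.
- A reader might take 24 as a hard maximum. The wording on added patients is a minimum, and replacements come on top.

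**The rates are assumed.** A flat DLT rate over doses that rise 16-fold (0.5 to 8 × 10⁹ cells) is a convenience. The percentages depend on it; the counts in steps 1 to 3 do not.

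**Conclusion.** The stated size is wrong as written, because 12 at three per tier matches section 7.4 only when no cohort is added anywhere. Two results need no assumption about toxicity: no path that completes all four tiers yields an MTD within 12, and the outcome of 0 of 3 at Tier 4 has no decision rule. The frequencies (MTD within 12 in about 3%, 10% and 23% of trials; more than 12 treated in about 40%, 52% and 40%) rest on the assumed flat rates, independent patients and no replacements. The fault is an inconsistency in the stated size and in the claim about the MTD, not a failure of the safety objective. It should be corrected because the enrolment figure, the cohort rules and the MTD definition are all fixed in this protocol.

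**What to change.** 1. In the Study Summary, Treatment Schema and sections 1.9 and 4.1, describe 12 (n=3 per tier) as the count when no DLT occurs and no MTD is declared.
2. State that the section 7.4 cohort rules can take the number treated to 24 (4 × 6), or more with replacements and with the at-least-three wording. State that 21 or 24 treated exceeds the 20 consents, and align that ceiling.
3. Reconcile the section 7.4 table and MTD definition with the n=3 tiers by saying what is concluded after 0 of 3 at Tier 4. Which rule applies there is for the sponsor to decide.
4. If no MTD can be declared there, limit the claim to the highest tier given, with its DLT count and exact two-sided 95% upper bound (70.8% for 0 of 3).

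Deleting the MTD text alone would not be enough: the 1-of-3 expansion would remain, and on a path through Tier 4 it still gives 15.

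The cost is wording and a less favourable claim.

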#### 4.1 General Design

This is an open label, single-center phase I study of TRACT in living donor renal transplant recipients. This safety portion of this study will continue for six months but the patients will be followed for up to 60 weeks. Participants will receive “standard of care” immune suppression, living donor kidney transplantation and TRACT. Prior to the kidney transplant, blood will be collected for immunophenotypic analysis of circulating leukocytes by flow cytometry, as well as functional immune assays. **Dose escalation of nTregs will be based upon the absence of infusion related side effects and specific adverse events (subsequent rejection episodes, allosensitization, development of opportunistic infection) within 30 days of infusion.**

Patients will undergo living donor kidney transplantation using immunosuppression based upon the standard of care regimen using alemtuzumab and the avoidance of oral corticosteroids (46, 47). This immunosuppressive regimen has been used for more than a decade at Northwestern in more than 2000 kidney transplant recipients. All patients will receive two doses of alemtuzumab (Campath-1H, 30mg); one at the time of renal transplant, and one on post-operative day two to achieve peripheral T-cell depletion. Intravenous glucocorticoids will be administered prior to Campath administration to limit cytokine release syndrome in association with this monoclonal antibody, and continued for the first two days post-transplant. Thereafter, steroids will not be used for immunosuppression. All transplant recipients will be started on oral immunosuppressive therapy with MPA and tacrolimus prior to transplant. After 30 days, patients will be converted to the combination of Sirolimus and MPA, as the inhibition of IL2 production by CNIs would impair the survival of infused expanded Tregs.

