## SCHEDULE OF EVENTS: SAMPLE COLLECTION FOR TRACT STUDY

[figure not shown]

Escalating doses of autologous expanded Tregs (TRACT) will be administered to the next cohort of patients if there are no observed serious adverse events within 30 days of TRACT infusion as follows:

Tier 1:  $0.5 \times 10^9$  total expanded Tregs (n=3)

Tier 2:  $1 \times 10^9$  total expanded Tregs (n=3)

Tier 3:  $5 \times 10^9$  total expanded Tregs (n=3)

Tier 4:  $8 \times 10^9$  total expanded Tregs (n=3)

Patients will be monitored at various time points, as described above for evidence of donor-specific transplantation tolerance using in vitro analyses, specifically mixed-leucocyte reaction assays (MLR). Graft function will be monitored clinically in the standard fashion. The overall goal for this phase I study is to demonstrate the safety of TRACT administration in kidney transplant recipients, and lay the foundation for a subsequent phase 2 trial. If we are successful, this approach could have for a transformative effect upon the field of solid organ and cellular transplantation.

The clinical site for recruitment, enrollment, and treatment of patients will be Northwestern Memorial Hospital. The Principal Investigator is part of a team with the most active living donor renal transplant program in the nation, with more than 160 such transplants performed in 2011. There already exists a robust infrastructure for combined therapeutic cell transfer (stem cell) and solid organ transplantation with two protocols for living donor renal transplants + HSC having been active at Northwestern for almost 5 years; [name], the IND sponsor and co-investigator, serves as PI or co-PI on these trials (50, 51).

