## **7.4 Dose Limiting Toxicity (DLT) Determination in the Study**

This is an open-label, single arm, dose escalation- de-escalation, phase I safety study which will examine the feasibility and safety of infusing autologous regulatory T cells (Tregs) into patients who have received a living donor kidney transplant. Tregs will be administered approximately 60 days post kidney transplantation.

According to the phase I dose escalation/de-escalation study design described below. The 4 dose levels are:  $0.5 \times 10^9$ ,  $1 \times 10^9$ ,  $5 \times 10^9$ ,  $8 \times 10^9$  Treg cells. All patients will be observed for a minimum of four hours following infusion and cell related toxicities monitored for the next three weeks. Patients with grade 3 or 4 toxicity during the infusion will have their cellular administration discontinued immediately and the event noted as a dose-limiting toxicity.

Adverse event information from the infusion will be used to determine whether the next subject within each cohort will receive the dose of cells associated with that dose level. The PI, IND Sponsor, IND Medical Monitor and study co-investigators will review toxicity reports and recommend whether or not it is safe to proceed at this dose level for the next patient. The next patient within a dose level will only be administered Treg after the first patient has been followed for at least 21 days and no evidence of dose limiting toxicity has been seen. The dose level for a given patient and the progression of doses from one cohort of patients to the next will be adjusted based on adverse events.

Adverse event information from the infusion will be used to determine whether or not dose escalation or de-escalation to the next level will occur. Adverse events will be graded using the Common Toxicity Criteria for Adverse Events, version 4.0e (NCI-CTCAE v4).

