## 7.5 Stopping Rules

The Principal Investigator may terminate the trial after consultation with the appropriate consulting staff at any time.

Patients with grade 3 or 4 toxicity during the infusion will have their cellular administration discontinued immediately and the event noted as a dose limiting toxicity.

The study as a whole will be halted if 2/5 patients develop grade 3-4 infusion reactions, or grade 4 organ toxicity within the first 30 days following Treg infusion. The study will also be halted if a death results from any of the criteria listed above.

If two of three consecutive subjects receiving experience severe steroid resistant acute rejection, vascular acute rejection, graft loss, malignancy, severe infection, and/or death in a period of 3 months, enrollment will be stopped and the study reassessed by the investigators, the IND sponsor and IND medical monitor.

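### Section 7.4 holds the escalation review at 21 days while 4.1 asks for 30 rejection-free days, and neither requires the 3-month biopsy result that would show rejection

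*Protocol*

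**What the plan says.** Section 7.4 sets the waiting period between dose levels: "Dose escalation will only occur after patients, at a given dose level, have been followed for at least 21 days" without a dose-limiting toxicity (DLT). It adds that "enrollment into the next dose level will only begin after all patients in that cohort have passed through the DLT observation period", and the investigators, IND sponsor and medical monitor review toxicity reports then. A DLT must occur in the first 3 weeks and be judged unrelated to the kidney transplant. Within a level, "The next patient within a dose level will only be administered Treg after the first patient has been followed for at least 21 days". On timing, "Tregs will be administered approximately 60 days post kidney transplantation".

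Section 4.1 sets a longer condition. Escalation rests on the absence of infusion-related side effects and of specific adverse events: "subsequent rejection episodes, allosensitization, development of opportunistic infection) within 30 days of infusion". Under the Schedule of Events heading, the next cohort is dosed if there are "no observed serious adverse events within 30 days of TRACT infusion".

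Section 3.1 includes, within the primary objective, finding out whether the cells lead to rejection. Section 7.3.3 requires biopsy confirmation of every rejection and schedules protocol biopsies at 3 months and 1 year; 7.3.2 gives the same two times.

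Section 7.5 stops enrollment on a narrower list, counted over 3 months: "If two of three consecutive subjects receiving experience severe steroid resistant acute rejection, vascular acute rejection, graft loss, malignancy, severe infection, and/or death".

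**The concern.** Rejection is a named escalation criterion in 4.1, and biopsy is the protocol's required means of confirming it. If the review in 7.4 is held when the 21-day window closes, the decision to raise the dose can be taken before the only scheduled test for that criterion has been done in every subject of the cohort. The step being decided can be five-fold (Tier 2 to Tier 3, 1 to 5 x 10^9 cells).

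Clinical rejection may well be seen earlier. Section 7.3.2 lists blood chemistry at weeks 10 and 12, which can prompt a for-cause biopsy. What the review can miss is therefore mainly rejection without a rise in creatinine, which is what a protocol biopsy adds.

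Because 7.4 and 4.1 give different waiting periods, the team conducting the trial also has to decide which one controls.

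**Working it through.** The plan gives no figure for the interval from infusion to biopsy, so there is none to reproduce. Inputs:

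- infusion on day 60 (4.1)
- DLT window of 21 days (7.4)
- escalation condition of 30 days (4.1)
- first protocol biopsy at 3 months (7.3.2, 7.3.3)
- three subjects per tier (4.1)

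**One subject.**

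- DLT window closes: 60 + 21 = day 81.
- 4.1 window closes: 60 + 30 = day 90.
- Biopsy at week 12: day 84, which is 84 - 60 = +24. That is 3 days after day 81 and 6 days before day 90.
- Biopsy at three calendar months: day 89 to 92, which is +29 to +32. That is 8 to 11 days after day 81, and from 1 day before to 2 days after day 90.
- Chemistry at weeks 10 and 12: days 70 and 84, or +10 and +24. Only the first precedes day 81.

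**A cohort of three at minimum spacing**, in days from the first infusion.

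| Stagger | Infusions | 7.4 review | Biopsies, week 12 | Biopsies, calendar | Outstanding at 7.4 review | 30 days complete |
|---|---|---|---|---|---|---|
| Each subject waits for the one before | 0, 21, 42 | 42 + 21 = 63 | 24, 45, 66 | 29-32, 50-53, 71-74 | 1 of 3 | 42 + 30 = 72 |
| Only the first is followed alone | 0, 21, 21 | 21 + 21 = 42 | 24, 45, 45 | 29-32, 50-53, 50-53 | 2 of 3 | 21 + 30 = 51 |

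With a 30-day wait, none is outstanding if the biopsy is at +24, +29 or +30. At +31 or +32, the same one or two subjects are outstanding, for 1 or 2 days.

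**Exposure at the new level.** Suppose its first subject is infused on the day of the 7.4 review, 21 days after the previous cohort's last infusion. The stagger puts the second at 21 + 21 = 42 days or later. All earlier biopsies are due by +32, so about one subject is exposed early.

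**Infusion later than day 60.** The biopsy still follows the 21-day window for infusion up to day 62 (biopsy day 84), day 67 (day 89) or day 70 (day 92).

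**Chance of a hold if the biopsy counts.** The documents give no rejection rate for the 3-month biopsy, so rates are assumed and subjects taken as independent. Per cohort the chance is 1 - (1 - p)^3; over the three escalations (9 subjects) it is 1 - (1 - p)^9.

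| Assumed p | Per cohort | Three escalations |
|---|---|---|
| 5% | 14% | 37% |
| 10% | 27% | 61% |
| 15% | 39% | 77% |

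**The case against.** The strongest reply is that 21 days in 7.4 is a minimum. Read together with 4.1, both conditions apply and day 30 controls. The schedule also suggests that month 3 is week 12: week 12 is a listed visit, and visits change from weeks to months after week 24. A week-12 biopsy at +24 lies well inside the 30-day window, so rejection on it could bar escalation as written. This stands, and it limits the point. It does not remove it, because 7.4 places its review at the end of the DLT window and no section makes the biopsy result a condition.

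Second, discretionary review exists. Section 7.4 says that "the progression of doses from one cohort of patients to the next will be adjusted based on adverse events", and 8.1 and 9.4 add weekly review and a review before each escalation. These can act on a biopsy already read, but none obliges the group to wait for one.

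Third, if enrollment in 7.4 means consent before transplant, the next infusion comes some 60 days later and no one is exposed early. That is possible, but 7.4 also sets dose escalation itself at 21 days, so the reading is not secured.

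Fourth, 6.3 bases the diagnosis of rejection on clinical signs and laboratory tests, confirmed by biopsy. A finding on histology alone may therefore not count under 4.1 on any day. That is fair, and it is a reason to say explicitly whether it does.

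A reader might infer that most biopsies fall outside the 4.1 window, so that one finding bars escalation on day +30 and is ignored on day +31. The documents do not support that. It needs exact calendar months and infusion on exactly day 60, whereas 7.4 gives the infusion day only approximately and a week-12 reading removes the cut-off problem for this biopsy. The schedule-of-events figure is not available to settle it.

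**Conclusion.** The point holds in limited form. Sections 7.4 and 4.1 give different waiting periods, 21 and 30 days. With infusion on day 60, the 3-month biopsy follows the end of the 21-day window on either reading, by 3 days or by 8 to 11. The 7.4 review can then precede the biopsy of one or two of the three subjects. If 4.1 controls, the gap is nil or at most about 2 days.

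A reader might infer that a whole cohort could receive the higher dose before these results exist, or that milder rejection found after day +30 cannot be acted on. Neither follows: the stagger limits early exposure to about one subject, and discretionary review remains even though 7.5 lists only the more severe outcomes.

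The conclusion assumes minimum spacing and infusion on or close to day 60; a later infusion can reverse the order. It is an inexpensive improvement in safety before a step of up to five-fold, and does not show the design to be unsound.

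**What to change.** In 7.4, replace the 21-day wait between dose levels with the 30-day condition of 4.1, and require the 3-month protocol biopsy result of every subject in the cohort to be available at the escalation review. State that biopsy-proven rejection on that biopsy counts as a 4.1 rejection episode even if the biopsy falls a few days after day +30, and that the review group decides how a hold is resolved. The 21-day DLT definition, the stagger within a cohort and the 7.5 thresholds can stay.

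This needs a protocol amendment and no new procedure. Waiting for the biopsy alone adds 3 to 11 days per cohort to the 21. With 30 days as the floor the addition is 9 to 11, of which 4.1 already asks for 9. The net extra is therefore at most about 2 days, plus pathology reporting time, which the protocol does not give.

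The larger cost is a hold caused by background rejection. Section 2.3 cites an incidence of acute rejection below 10% on the center's regimen, without a time frame, and the table in the working shows that a hold at some point in the trial would not be rare at such rates. Section 4.1 already has this effect for any rejection found by day +30, so the change settles the cut-off and does not set a stricter threshold.
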